### Statistical analyses

Sample size was calculated using nQuery (version 3.0; Statistical Solutions, Cork, Ireland) prior to the start of this *in situ *study. To determine an appropriate specimen quantity to achieve an adequate power of 80% and a defined significance level of 5% (p < 0.05), the number of participants was determined to be 38 (in anticipation of a dropout rate of 10%). The expected mean value of mineral loss was 200 vol% × μm with a standard deviation of 400 vol% × μm. These values were calculated taking into account the ascertained values of previous *in vitro *studies [27,33]. In detail, those studies gave informations about the required contact time between specimens surface and saliva substitute *in vitro*, thus these results served as base for determining the specimens *in situ *contact time storage. After transversal microradiography evaluation and collection of the questionnaires, statistical analyses will be conducted using a *t*-test for paired samples. In the case of non-normally distributed values, we will apply Wilcoxon's signed-rank test. Commercially available software (PASW for Windows, version 18.0; SPSS, Munich, Germany) will be used for all statistical computing.

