## Methods/Design

### Experimental design and study population

This study is performed at the Department of Operative Dentistry and Periodontology, University School of Dental Medicine, CharitéCentrum 3, Charité - Universitätsmedizin Berlin, Germany. A controlled, randomized, crossover, double-blind, phase II/III *in situ *trial design is conducted with volunteers who are residents of Berlin. All participants are clinically evaluated by a detailed dental examination and an unstimulated salivary flow rate measurement. Before participating in the study, volunteers are informed concerning the objectives, benefits, and possible risks involved in the study. The research team provides an informed consent form that includes the study details, such as purpose, duration, required procedures, possible advantages, and key contacts. The main inclusion criterion (Table 1) is an unstimulated whole saliva flow of ≤ 0.1 ml/min. Furthermore, one removable dental prosthesis (upper or lower denture) and an age over 18 years are required. Panelists are accepted for study participation only after signing the informed consent forms. The trial period is divided into two phases, and each phase consists of seven weeks with a washout period of seven days between the phases (Figure 1). The volunteers are randomly allocated into two groups. In each study leg, the participants are submitted to treatment with one of the two saliva substitutes (Figures 1 and 2).

**Table 1 T1:** Inclusion and exclusion criteria

Inclusion criteria	Exclusion criteria

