**Figure 2 F2:**
[figure not shown]
**Study design**. t0: - Integration of specimens into removable (partial) dentures Covering of reference areas/sound surfaces of specimens - Issue of study medication (blinded) - Anamnesis and oral findings - Measurement of unstimulated saliva flow rate - First questionnaire. t5: - Covering of effect areas after five weeks - Measurement of unstimulated whole saliva. t7: - Removal of specimens from the dentures - Measurement of unstimulated saliva flowrate - Second questionnaire - Collecting of spray bottles. t8: - Integration of specimens into the removable (partial) dentures - Covering of the reference areas/sound surfaces of specimens - Issue of study medication (blinded) - Anamnesis and oral findings - Measurement of unstimulated saliva flowrate - Third questionnaire. t13: - Covering of effect fields after five weeks - Measurement of unstimulated saliva flowrate. t15: - Removal of specimens from dentures; repair of dentures - Measurement of unstimulated saliva flowrate - Last questionnaire - Collecting of spray bottles

The randomization process was performed externally by the Department of Biometry and Clinical Epidemiology (CharitéCentrum 4, Berlin, Germany) using a computer-generated random table (Microsoft Excel, Unterschleißheim, Germany). The investigators were not involved in the randomization process, nor were they aware of the assigned group in any of the outcome evaluations. The identification codes for each panelist were printed on the bottle labels at Charité's pharmacy.

A dental study nurse is commissioned to allocate the sealed envelopes, which contains the blinded saliva substitutes from the pharmacy. This procedure guarantees a continuous medication blinding process for both panelists and investigators. After each testing phase, all of the released bottles are collected by the clinical investigators to determine consumption based on weight. The volunteers wear removable dentures comprising four inserted specimens during each study phase (2 enamel and 2 dentin specimens) (Figures 3 and 4d). All of the specimens are obtained from one bovine tooth. Furthermore, the enamel specimens are divided into two subgroups, including sound and artificially demineralized (subsurface lesion) enamel (Figures 3b, c and 4).

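### The planned paired t-test and signed-rank test leave phase out of a two-sequence crossover, so any systematic phase difference costs power and, if the sequence groups end up unequal, shifts the estimate for that split

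*Protocol article*

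**What the plan says.** Under Experimental design and study population, the Protocol article describes a crossover in which "each phase consists of seven weeks with a washout period of seven days between the phases". It adds: "The volunteers are randomly allocated into two groups". Each patient uses one substitute per phase, modified Saliva natura (SN) or Glandosane (G), so the two groups are the two treatment orders.

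The text on randomisation that follows the Figure 2 legend says the allocation was produced externally, "using a computer-generated random table (Microsoft Excel" being the stated tool.

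Under Statistical analyses, one test is named for microradiography and questionnaires alike: "After transversal microradiography evaluation and collection of the questionnaires, statistical analyses will be conducted using a *t*-test for paired samples". The fallback is: "In the case of non-normally distributed values, we will apply Wilcoxon's signed-rank test". Nothing in the article mentions a phase (period) or sequence term. The planning figures in the same section are "an adequate power of 80% and a defined significance level of 5% (p < 0.05"), 38 participants allowing for 10% dropout, and: "The expected mean value of mineral loss was 200 vol% × μm with a standard deviation of 400 vol% × μm".

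**The concern.** A paired test pools all SN minus G differences as if they came from one population. In a two-sequence crossover they come from two. Patients who receive SN second carry the phase effect with a plus sign, and those who receive SN first carry it with a minus sign. If phase 2 differs systematically from phase 1, the pooled differences are more spread out than they need be. If the two groups differ in size, the plus and minus signs do not cancel.

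Two features of the study make a systematic phase difference plausible:

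- **Diet and hygiene.** The fluoride-free hygiene and the avoidance of sour and fluoride-containing food belong to the study. Phase 1 therefore starts from usual habits, while phase 2 starts after patients have already spent seven weeks under study conditions.
- **Questionnaire baselines.** The first questionnaire precedes any study product. The one at week 8 follows seven weeks on one substitute and one week off it.

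At stake is the precision of the SN versus G contrast, which is the purpose of the trial. The information needed to remove a phase effect already exists, because order is randomised.

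This is not a detail left to an unseen analysis plan: the article names a specific test, and that test discards the sequence.

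**Working it through.** **Inputs.** From Statistical analyses: mean 200, SD 400 (vol% × μm), power 80%, alpha 5%, 10% dropout, N = 38. Assumed: a two-sided test, and 200 and 400 as the mean and SD of the within-patient difference. The phase effect π (phase 2 minus phase 1) is not in the document; 100, 200 and 300 are used as a range.

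**Step 1: the plan's own figure.** For a two-sided paired t-test with effect/SD = 200/400 = 0.5, n = 33 gives 79.5% power and n = 34 gives 80.8%. Then 34/0.9 = 37.8, rounded up to 38. The stated N is reproduced, which supports this reading of the inputs.

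**Step 2: what the paired test estimates.** Let τ be the SN minus G effect, n1 the number who receive SN second and n2 the number who receive SN first. The differences have mean τ + π in the first group and τ − π in the second. The pooled mean has expectation τ + π(n1 − n2)/(n1 + n2).

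**Step 3: equal groups, 17/17.** The bias is zero. The SD of the pooled differences rises to about √(400² + π²), and the standard error is that SD divided by √34 (68.6 without a phase effect). Power and type I error are simulated.

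| π | SD | SE | Paired power | Paired type I error | Adjusted power |
|---|---|---|---|---|---|
| 0 | 400 | 68.6 | 81% | 5.0% | 81% |
| 100 | 412 | 70.7 | 79% | about 4.3% | 81% |
| 200 | 447 | 76.7 | 73% | about 2.9% | 81% |
| 300 | 500 | 85.7 | 64% | about 1.4% | 81% |

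**Step 4: unequal groups, conditional on the split, π = 200.**

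- 20/14: bias 200 × 6/34 = 35; type I error stays near 5%.
- 21/13: bias 200 × 8/34 = 47, which is 24% of the planned 200; type I error 6.8%.

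The sign of the bias follows the direction of the imbalance. If 34 patients were allocated by simple 1:1 randomisation, a difference of 6 or more between the groups has probability 0.39, and of 8 or more 0.23.

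**Step 5: averaged over simple randomisation.** If the split is drawn at random in each run, mean bias is about 0 and type I error is about 5% for π = 100, 200 and 300. Power at π = 200 is about 71–72%.

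**Step 6: the adjusted test.** Half the difference between the sequence means of the within-patient phase differences estimates τ and is free of π. Its standard error is (400/2)√(1/n1 + 1/n2), with 32 degrees of freedom.

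- 17/17: SE 68.6, power 81%
- 20/14: SE 69.7, power 79%
- 21/13: SE 70.6, power 78%

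Type I error is 5% whatever π is. At 17/17 this test still needs 34 evaluable patients, hence 38 enrolled.

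**The case against.** The strongest reply is that the harm is conditional and may be small. The document gives no phase effect. At zero the paired test is valid, and at 100, half the planned treatment effect, balanced power is still 79%. A phase effect of 200 would be as large as the treatment effect the trial is sized for. All of this stands, and it limits how serious the point is.

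A reader might infer that the planned test is biased or raises the false-positive rate. The document does not support that as a general statement. With equal groups the test is conservative. Over simple randomisation the bias averages to zero and type I error stays near 5%. Type I error rises above 5% only after conditioning on a marked imbalance such as 21/13.

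Three further inferences also go too far:

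- **No blocking.** The article does not mention it, but a condensed article commonly omits such detail, and an external biometry department did the randomisation. Lack of balance cannot be read from silence. Even a blocked list, however, can become unequal through dropout.
- **A new tooth in each phase, and varying diet or saliva, as phase effects.** These are mostly random within-patient variation, which a phase term does not remove. Mineral loss is also referenced to covered areas of the same specimen. Only a shift common to one phase counts; the study regime and the questionnaire baselines are the better candidates. Whether the regime continued through the washout is not stated.
- **Normality checked on raw measurements.** The fallback sentence speaks of values without saying which, and in a sentence about paired tests the paired differences may be meant.

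**Conclusion.** The point holds as a stated but inefficient choice of analysis, and should be fixed. The named tests omit phase in a design that randomises order.

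The expected cost is power. With 34 completers, equal sequences and an SD of differences of 400, it amounts to about 2, 8 and 17 percentage points for phase effects of 100, 200 and 300. When the achieved sequences are unequal, the estimate is additionally shifted for that split, by 47 vol% × μm in the 21/13 example at a phase effect of 200.

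These sizes rest on reading 400 as the SD of the within-patient difference, which reproduces the stated N, and on phase effects that are assumed, not documented. The microradiographic figures do not carry over to the questionnaire scores, for which the article gives no planning values.

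**What to change.** Before unblinding, replace the paired t-test with the standard analysis of a two-sequence crossover. Either of these forms will do:

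- a two-sample t-test comparing within-patient phase differences between the two sequences, halving the estimate to give the SN minus G effect; or
- a linear mixed model with treatment, phase and sequence as fixed effects and patient as a random effect.

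The two are equivalent for complete pairs only. The mixed model can also use patients who finish a single phase. As the non-parametric form, replace the signed-rank test with the Wilcoxon rank-sum test on within-patient phase differences between sequences.

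The Results section says that evaluation awaits the last participant and that allocation remains blinded, so the change can still be made without knowledge of the results by treatment.

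The cost is wording, one degree of freedom, and slightly lower power when sequences are unequal and there is no phase effect: about 79% at 20/14 and 78% at 21/13, against 81% for the paired test. No further data are needed, and N stays at 38.

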## Results

Hitherto, 14 patients with oral dryness who reside in Berlin have been recruited for the present study. These patients completed both test phases (Figure 1). Up to now, no reasons for early termination of the trial have been identified. Therefore, evaluation of the data will be performed after recruitment of the last participant. For this reason patient/specimen allocation will remain blinded.

## Discussion

Hyposalivation is mostly associated with various syndromes, diabetes, vitamin deficiency, menopause, salivary gland hypofunction due to inflammation, infection, the use of various drugs, or radiotherapy. Since incidence of head-and-neck cancer [35] and amount of drug revenue increases with age, primarily older patients suffer from hyposalivation [36]. Furthermore, periodontal diseases occur predominantly in elderly patients and often lead to gingival recessions [37]. Additionally, progressive attrition/abrasion during prolonged utilization of the teeth causes dentin exposure [38]. Since dentin is not as resistant as enamel to acid exposure, earlier and more severe demineralization can be expected [39]. Thus, carious lesions located at the cervix of the teeth develop easily during radiation therapy [40,41]. Therefore, in the present study, both enamel and dentin were assessed.

The teeth used in the present study were obtained from newly slaughtered cattle. One of the major disadvantages of human teeth compared to bovine teeth is the occurrence of defects such as initial carious lesions. It can be assumed that bovine teeth are rarely influenced by external factors (*e.g*., acids, fluorides), and, thus, the biological spread of bovine teeth is relatively small [25,42]. In contrast, human teeth usually exhibit an inconsistent age and source, which might result in a variable composition that leads to larger variations in the test response. Due to their similar chemical composition, general availability and large size, bovine teeth are a suitable substitute for human dental hard tissues in *in situ *examinations, and a more uniform reaction can be expected using these specimens [42]. Moreover, lesion formation in bovine enamel is very similar to the demineralization process observed in human enamel [25]. However, bovine enamel is generally considered a more porous material compared to human enamel, and, thus, bovine enamel may be susceptible to accelerated demineralization [43]. For *in situ *studies into caries prevention, sterilization of tooth specimens is essential. Sterilization of enamel and dentin using ethylene oxide has not been considered to induce relevant effects with *in situ *studies of de- and remineralization [44].

As a precursor of dental caries, initial subsurface lesions appear in many patients [1]. These lesions were simulated in the present study by the artificial demineralization (*i.e*., subsurface lesion) of half of the enamel specimens before *in situ *incorporation. Furthermore, an investigation of the remineralization processes requires the utilization of artificially demineralized enamel specimens that are adjacent to sound specimens. Due to the possibility of disintegration during the *in situ *exposure, the dentin specimens were not artificially demineralized. Four specimens that were obtained from one bovine tooth were embedded into the removable denture of one patient during each experimental phase (Figures 3a and 4). This procedure ensured that the specimens from one tooth were only used for one patient and that one bovine individual-to-one patient regimen was maintained. Furthermore, the enamel and dentin specimens correlated with respect to their source during each test phase, and this permitted a comparison of the *in situ *effects of demineralization and remineralization between dentin and enamel.

To investigate the effects of the study medication on the specimen surfaces after a wearing period of five and seven weeks, the surfaces were divided as described (Figure 3). By covering the respective surface areas with acid-resistant nail varnish and a flowable composite, the sound and artificially demineralized regions were maintained during the entire *in situ *investigation for the microradiographic analyses. Additionally, the coverage of the effect fields (E1; Figure 3) after five weeks ensured that this surface areas were not affected by additional de- and remineralizing effects. This method allowed the determination of distinguishable test areas.

Specimens attached on natural teeth could interfere with mastication and articulation, and, therefore, specimens were fixed in removable dentures. However, it has to be taken into account that wearing a dental prosthesis (full or partial) can significantly affect the composition of the resident oral microflora, and, following, the results might be influenced by this factor [45]. Therefore, this factor should be kept in mind when interpreting the upcoming data. Unlike former *in vitro *studies [46], the coverage areas were additionally fixed with flowable composite to ensure the ability to withstand mechanical forces during the study period. Up to now no visible gaps between the specimen surfaces and the coverings have been recognized. Moreover, the additional test field coverage with composite resin seems to be advantageous for protection of surface areas. So far no coverage losses could be observed.

The intention of the chosen *in situ *model was to mimic the natural caries process and provide clinically relevant information in a relatively short period of time without causing irreversible tissue changes in the panelists' dentition. Generally, clinical caries trials are limited to investigations by a dental explorer, and to using radiographs to identify and validate demineralizations at sites usually not visible directly. Thus, the caries process is determined at a relatively late stage and patients are exposed to X-rays resulting in an increasing radiation exposure. In contrast, the *in situ *model presented here offers the integration of transversal microradiography (TMR) as a basic science analytical technique. TMR offers high sensitivity and ensures waiving radiation exposure for panelists [47]. Generally, various experimental methods are available for analyzing subsurface lesions of bovine enamel and dentin specimens. These include transversal microradiography [48], polarized microscopy [49], microhardness testing [50,51], electric caries monitoring [52], transversal wavelength-independent microradiography [53], optical coherence tomography [54], and scanning electron microscopy [55,56]. With the exception of transversal microradiography (TMR), all mentioned technologies reveal some shortcomings with regard to accuracy when specimens are analyzed according to the mentioned parameters mineral loss and lesion depth. In contrast, TMR allows a direct measurement of the longitudinal mineral distribution as a profile in a subsurface lesion and has long been established and recognized as a gold standard for analyzing mineral content changes over time [57]. Consequently, TMR is considered a surrogate outcome measure that is directly impacted by the intervention. Thus, microradiographic outcome was selected as a surrogate endpoint in the present study.

Since fluorides are commonly found in foodstuff such as salt, fish, and mineral water, the study implementation required a renunciation of several foods in terms of a fluoride-free diet. This adjustment was only established for the (short) *in situ *period, and thus, might represent a lower personal burden for the patients compared with long-term clinical trials [47]. Altogether, an *in situ *model might better conform with the patients' requirements, and these always have to be weighed against the background of protracted cancer-related therapies.

Saliva substitutes such as the widespread Glandosane, which contains acids and a relatively low amount of calcium and phosphates (and, therefore, is undersaturated with respect to calcium phosphates), have demonstrated demineralizing properties *in vitro *[1,25,26,33]. From the perspective of dental medicine, neutral or even remineralizing effects of artificial salivas would seem preferable [48]. Glandosane has a pH value of 5.3, whereas the pH value of the modified SN is approximately 5.98. Due to the strict permission criteria for the modification of existing saliva substitutes (German Act of Medical Devices), a higher pH value could not be adjusted for SN. Even solutions with low pH values or a large amount of titratable acids do not cause demineralization in dental hard tissues, if an appropriate saturation is used with respect to relevant calcium phosphates via a reduction of the apatite solubility [58]. In previous *in vitro *studies, supersaturated solutions such as modified SN was observed to remineralize enamel and dentin over a period of five weeks, and this has been attributed to the addition of calcium, phosphates and fluorides [33]. Human saliva can be considered a supersaturated solution with respect to hydroxyapatite (HA), and has a mean pH value of 6.7 under physiological conditions [1]. In addition to flushing purposes, saliva also acts as a buffer. Bicarbonate and phosphate buffers in particular allow for neutralization of organic acids via diffusion through the dental plaque. The saliva of patients who suffer from hyposalivation after radiotherapy reveals a decreased pH value (*i.e*., acidic pH value), which promotes the demineralizing processes of dental hard tissues.

The primary component of enamel is HA. The solubility of a substance is characterized by its solubility product (K). For a solution such as saliva, the ion product (IP) is based mainly on the calcium, phosphate, and hydroxyl concentrations. The thermodynamic driving force of enamel de- or remineralization is a function of the degree of saturation with respect to HA (DS_HA_) [59,60], and the degree of saturation of a solution (DS) can be defined by dividing the product of the ion activities (IP) by K, and exposing this result to the number of ions in the formula unit [61]. If DS is greater than 1, the solution is supersaturated with respect to the calculated mineral phase; if DS is less than 1, the solution is undersaturated; in case of DS equals to 1, the solution is saturated, and no net dissolution or precipitation occurs. For aqueous solutions, the degree of saturation with respect to apatites [HA, octacalcium phosphate (OCP), dicalcium phosphate dihydrate (DCPD), and calcium fluoride (CaF_2_)] can be calculated, if the pH and the concentrations of certain ions are known [62]. In a previous study [27] that determined the composition of the SN used in the present one, IONPRODUCT, which was developed by Peter Shellis [62], was used. IONPRODUCT is a computer program that calculates the ionic activity of products and the degree of solution saturation with respect to biologically relevant calcium phosphates. The input values are the concentrations of the constituent ions, pH, temperature, and atmospheric pressure. A database contains the required solubility products of each of the minerals and the relevant dissociation constants. The program can be used to determine the DS at different pH values for a given calcium concentration.

Because patient acceptance of slightly acidic saliva substitutes is higher compared to products with neutral pH values, the current pH values of SN as well as of G might support patient compliance [27,33]. In the present study, an experimental period of seven weeks was selected. The present test field design refers to former *in vitro *studies exhibiting effects after an investigation of five weeks [33,48,63]. Since artificial saliva was clinically administered *ad libitum*, no maximum daily dose could be assumed. These procedures, employed in previous *in vitro *studies, simulated an extremely intense contact between saliva substitutes and specimens during an experimental time of up to five weeks, and, hitherto, these conditions could not be replicated with clinical settings and conditions. Therefore, in comparison to former *in vitro *studies a longer examination time of seven weeks was selected.

It is important to note that unlike the conditions observed *in vitro*, a total absence of saliva is rarely observed in clinical situations. Due to a variable presence of saliva, compositional changes [15], and the decreased pH values detected in the present *in situ *study, slightly altered results should be considered. Despite the omission of factors such as nutrition, previous studies have noted the development of erosions on the specimen surface even under strictly controlled *in vitro *conditions. Variability in patient diets, especially the consumption of sour drinks/food, might lead to the development of erosion. To reduce the influence of diet on mineralization, the patients were provided with nutritional counseling. In the present study, the patients were asked to restrain from the consumption of any sour foodstuffs during the test period to avoid any bias. Furthermore, panelists' were asked to abstain from any additional intake of fluorides from food or any form of fluoride-containing oral hygiene products. Therefore, advisory information and nutrition counseling regarding fluoride uptake was conducted for all patients to illustrate the need of a fluoride-free diet. In particular, the panelists' were required to abstain from fluoride-containing toothpaste; instead, fluoride-free toothpaste was administered.

To receive the patients' personal assessment concerning their well-being and usage of salivary substitutes, questionnaires were handed out as described before (Figure 2). The simplicity of the questionnaires which was enabled by referring to the German school mark scale (1-6; 1 = very good, 6 = poor), being familiar to the patients, allowed for straightforward answers to the questions and provided a fast and simple evaluation by the investigators. The evaluated personal well-being and the self-assessed intensity of dry mouth before and after the use of each saliva substitute can be compared with each other and with the collected data containing measured values of the amount of natural salivation and saliva substitutes consumption during each trial. In addition, the questionnaires provide important information on the general acceptance of the use of saliva substitutes in terms of taste and duration.

Optimal oral hygiene and regular oral screening is necessary in individuals with hyposalivation due to an increased risk for caries and periodontal diseases. Saliva substitutes should not only relieve the symptoms of oral dryness, but should also provide protection against demineralization. In addition to other *in situ *studies investigating caries formation and the protective effect of fluorides, the present study is the first clinical trial to evaluate the effects of saliva substitutes on dental hard tissues *in situ*. It is difficult to control human behavior, and, therefore, the data which will be obtained herein might differ from those generated in previous *in vitro *studies. Despite these considerations, the present study has the potential to provide clinical data that can improve the effects of salivary substitutes and their acceptance among patients. Thus, the results of the present study should be important for future treatment guidelines for patients suffering from hyposalivation.
